#### Study outcomes

Prevalence and extent of albuminuria (uACR > 30 mg/g), hypertension (e.g., elevated blood pressure, Stage 1 hypertension, and Stage 2 hypertension), sickle cell trait and disease, hepatitis B & C infection, and Cytomegalovirus (CMV) infection, all stratified by HIV status.Prevalence of *APOL1* variants (high-risk (2 copies of *APOL1* risk variants) and low-risk (0–1 copies of *APOL1* risk variants), by HIV status.Proportion of ART-treated adults with suspected tubular albuminuria (urine albumin-to-protein ratio (uAPR) < 40%) [24, 25] as identified during Aim 1 cross-sectional evaluation.Proportion of ART-treated adults with suspected glomerular albuminuria (albumin-to-protein ratio (uAPR) ≥ 40%) [24, 25] as identified during Aim 1 cross-sectional evaluation

### Laboratory investigations

#### Albuminuria and proteinuria measurement

Urine biomarker assays (e.g., urine albumin, creatinine, and protein measurements) will be performed at the [name] laboratory (Brigham and Women’s Hospital Biomarker Laboratory, Boston, MA, USA) using the Randox Imola platform (Crumlin, UK) for urine creatinine measurement and the Randox Imola or BNII nephelometer platforms (Siemens, Malvern, PA) for urine albumin measurement ([name] laboratory). Specific urinary measures will be performed using the kinetic Jaffe method (creatinine), pyrogallol red colorimetry method (protein) and immunoturbidimetry (albumin) [78, 79]. Each participant will also provide a serum sample for creatinine, from which we will calculate eGFR using the 2021 CKD-EPI equation, specifically, the 2021 eGFR creatinine (Age and Sex (AS)) equation) [80, 81]. For quality control and assurance (QC/QA) purposes, we will utilize existing laboratory specimen handling and analysis standard operating procedures that we have developed and implemented in collaboration with the [name] laboratory team.

Each screened participant will be given a unique study ID number. The study subjects’ IDs can be linked back to participants and will be maintained in REDCap on study-specific secure (encrypted) tablets.

#### Genetics specimen collection and genotyping

Genotyping data are already available for participants who completed the screening phase of the R3 study. Dried blood spot (DBS) samples will be obtained for all newly enrolled participants. DBS samples for genotyping will be obtained by fingerprick, spotted (up to 125μL per each 1 inch application) on Whatman FTA cards (Whatman, Brentford, UK) using capillary tubes and subsequently dried at room temperature for 1 h. We will store the spotted Whatman FTA cards at room temperature (20–25° C) with a desiccant for humidity-control, and these cards will be shipped in batches to the Duke Molecular Physiology Institute (DMPI) Substrate Services Core Facility. Once at DMPI, using sterile biopsy punches, the team will take 6 mm punches from each dried-blood spot sample, with the filter card punch to be placed directly into an extraction tube, and the DNA isolated using Qubit DNA extraction kits (Thermo Fisher Scientific, Waltham, MA). Two elutions will be performed to increase the DNA yield, and DNA will be quantified using PicoGreen dsDNA Assays (Thermo Fisher Scientific, Waltham, MA, USA). For genotyping and sample handling, we will check 2.5–5% of duplicate filter papers for genotype match (and possibly run sex markers) for sex match between clinical record and genotypic sex.

*APOL1* genotyping will be performed in the [name] laboratory at the DMPI using TaqMan assays (San Diego, CA) targeting the 3 *APOL1* variants (rs73885319 [G1], rs60910145 [G1], and rs 71785313 [G2]) associated with CKD and HIV-associated kidney disease. The *APOL1* risk alleles are defined by G1 haplotypes (rs73885319-G/rs60910145-G and rs73885319-G/rs60910145-T) and the G2 haplotype (rs7175313-deletion). Testing for the chromosome 11 hemoglobin subunit beta (HBB) sickle cell variants HbS (rs334; p. Glu6Val) and HbC (rs33930165, p. Glu6Lys) will be performed using TaqMan assays. Other genetic loci associated with kidney disease or with susceptibility to infections may also be studied on an exploratory basis. We will define the *APOL1* genotype from the number of risk alleles. In recessive models, individuals exhibiting two risk alleles (G1/G1, G1/G2, or G2/G2) will be assigned to the high-risk (HR) group, while individuals carrying no or one risk allele (G0/G0, G0/G1, and G0/G2) will be assigned to the low-risk (LR) group. We will also perform exploratory analyses to examine the number of risk alleles (0, 1, or 2 alleles).

All information linking participants to personal identifiers will be destroyed once study follow-up and data analysis are completed. Individual participant data to be collected and maintained by de-identified study code include age, ethnicity, sex, occupation, weight, BMI, comorbid medical conditions (hypertension, diabetes, opportunistic infections, syphilis, cancer, cardiovascular disease, and other conditions of potential relevance to study outcomes), current ART regimen (for HIV-positive participants), and concomitant medications. Data on prior and current use of TDF, indinavir, and ritonavir-boosted protease inhibitors will be collected from HIV-positive participants and from review of the medical chart.

### Statistical considerations

#### Sample size

We enrolled 2500 PWH during the screening phase of R3. For these calculations, we assume a similar prevalence of albuminuria among the 500 participants newly recruited for this study. Of note, even if none of the 500 new recruits have albuminuria, the overall proportion among HIV-positive participants will be > 33%, and power calculations (i.e., detectable relative risks) are similar. Table 3 shows, for given sample sizes, the proportion of HIV-negative controls with uACR > 30 mg/g that we would be able to detect with 90% and 80% power at the alpha = 0.05 level (i.e., with a two-sided p-value < 0.05). For example, with 750 HIV-negative controls, we will have ~ 90% power to detect a relative risk for albuminuria between HIV-positive and HIV-negative participants of 1.19 (0.400 vs. 0.336, respectively).

**Table 3 Tab3:** Detectable proportion with microalbuminuria/macroalbuminuria with various sample sizes

Number of HIV-negative participants (N = 3000 HIV-positive participants)	Detectable proportion with micro-/macroalbuminuria among HIV-negative controls (RR = relative risk)	
	90% power	80% power
300	0.306 (RR = 1.31)	0.319 (RR = 1.25)
500	0.325 (RR = 1.23)	0.335 (RR = 1.19)
**750**	**0.336 (RR = 1.19)**	**0.345 (RR = 1.16)**
1000	0.343 (RR = 1.17)	0.350 (RR = 1.14)

Bolded numbers on far left (750) for each of these tables reflect our chosen final sample size for number of HIV-negative participants to be enrolled

In preliminary data from the R3 cohort, only 4% of participants were LTFU between the two uACR measurements. To account for LTFU, we conservatively estimate that we will need to recruit ~ 810 HIV-negative participants and ~ 540 newly enrolled HIV-positive participants (~ 8% LTFU). We plan to do analyses both categorizing uACR (> 30 mg/g) and treating it as a continuous variable. From our preliminary R3 study data, the mean uACR among HIV-positive adults was ~ 67 mg/g (standard deviation 266 mg/g). If our data are similarly skewed in this study, we will transform the data before analyzing. The mean log_10_ transformed uACR among HIV-positive adults was 1.35 log_10_ (mg/g) with SD = 0.554 log_10_(mg/g). Therefore, with n = 750 HIV-negative and 3000 HIV-positive participants, we anticipate having ~ 90% power to detect a difference in mean log_10_-transformed uACR between HIV-positive and HIV-negative adults of 0.132 standard deviations or 0.07 (i.e., 1.35 log_10_(mg/g) in HIV-positive vs. 1.28 log_10_(mg/g) in HIV-negative adults, corresponding to a median uACR of ~ 22.4 vs. 19.0 mg/g.

The calculations in Table 3 (and Tables 4 and 5) do not account for loss-to-follow-up (LTFU) between the two uACR measurements in the cross-sectional study. In our preliminary data, only 4% of patients were LTFU between the two measurements. Power is greater (although clinical interpretation may be more challenging) when uACR is treated as a continuous outcome. We plan to do analyses both categorizing uACR (> 30 mg/g) and treating it as a continuous variable. We therefore also present power evaluating uACR as a continuous outcome (Table 4). With 750 HIV-negative and 3000 HIV-positive participants, we will have ~ 90% power to detect a difference of 0.132 standard deviations between the mean outcome in HIV-negative vs. HIV-positive adults. From our preliminary data, the mean uACR among HIV-positive adults was ~ 67 mg/g (standard deviation 266 mg/g). This is quite skewed, so we will transform the data before analyzing. The mean log_10_ transformed uACR among HIV-positive adults was 1.35 log_10_ (mg/g) with SD = 0.554 log_10_ (mg/g). Therefore, with n = 750 HIV-negative and 3000 HIV-positive participants, we anticipate having ~ 90% power to detect a difference in mean log_10_-transformed uACR between HIV-positive and HIV-negative adults of 0.07 (i.e., 1.35 log_10_(mg/g) in HIV-positive vs. 1.28 log_10_(mg/g) in HIV-negative adults, corresponding to median uACR of ~ 22.4 vs. 19.0 mg/g.

**Table 4 Tab4:** Detectable mean difference for continuous outcome (in SDs) between HIV + and HIV- participants

Number of HIV-negative participants (n = 3000 HIV-positive participants)	Detectable difference between mean uACR in HIV-positive and HIV-negative participants (standard deviations)	
	90% power	80% power
300	0.196	0.170
500	0.157	0.135
**750**	**0.132**	**0.114**
1000	0.118	0.102

Bolded numbers on far left (750) for each of these tables reflect our chosen final sample size for number of HIV-negative participants to be enrolled

**Table 5 Tab5:** Interaction effects based on hypertension

Number of HIV-negative participants	Albuminuria prevalence for HIV-negative participants without hypertension	Albuminuria prevalence for HIV-negative participants with hypertension	Relative Risk (HIV-negative participants)
750	0.10	0.27	2.7
750	0.15	0.36	2.4
750	0.20	0.44	2.2
**750**	**0.25**	**0.50**	**2.0**

#### Power calculations for interaction effects

We will examine whether the association between risk factors and albuminuria differs between HIV-positive and HIV-negative participants. Table 5 illustrates the power for detecting interaction effects based on hypertension. From preliminary R3 data, 12.7% of our study participants had Stage 1 or 2 hypertension (JNC-7 classification). Overall, 47% of HIV-positive adults with hypertension had albuminuria, and 39% of HIV-positive adults without hypertension had albuminuria, for a relative risk of 1.22. If the prevalence of hypertension is ~ 10% among our HIV-negative participants, then Table 5 shows the relative risks among HIV-negative individuals for which we anticipate having ~ 80% power to detect based on varying prevalence of albuminuria. For example, with 750 HIV-negative adults and a true prevalence of albuminuria of 0.25 among HIV-negative adults who do not have hypertension, we have 80% power to detect a difference of relative risks for hypertension of 1.22 vs. 2.0 between HIV-positive and HIV-negative participants, respectively (Bold emphasis row, Table 5).

#### Statistical analysis plan

We will fit regression models based on categorized (i.e., logistic regression) and continuous (i.e., linear regression after log_10_ transformation and/or semiparametric cumulative probability models that empirically estimate the transformation) uACR levels [82]. HIV status is the primary exposure variable. We will perform additional analyses to investigate the interaction between HIV status and individual risk factors, including hypertension and co-infection (HBV and CMV), to determine whether associations differ based on HIV status (e.g., whether the impact of comorbidities on microalbuminuria is greater among PWH). Regression models will be adjusted for potential confounders, including age, ethnicity, smoking status, and BMI. Primary analyses will control for sex and will be repeated among men and women, separately, to investigate potential differences by sex. For the analyses limited to PWH, viral load (detectable/undetectable) will be included in models as a potential confounder. Missing data will be multiply imputed using standard techniques. Continuous covariates will be expanded using restricted cubic splines with three knots to avoid linearity assumptions. Additional analyses will be performed in the subset of HIV-positive adults to assess the association between HIV-specific factors (e.g., TDF exposure, duration on ART, detectable viral load, and CD4 cell count) on albuminuria/uACR (Additional file 1 and Additional file 2).

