#### Genetic analysis plans

We will determine the prevalence of *APOL1* risk alleles, comparing the 750 HIV-negative adults to our 3000 HIV-positive study participants, specifically comparing the proportions of each population (i.e., HIV-negative vs. HIV-positive) possessing 0, 1, and 2 *APOL1* risk haplotypes (G1 or G2). We will examine the association between *APOL1* genotype and uACR and eGFR, adjusting for sex, age, and HIV status. Furthermore, we will test whether the associations between *APOL1* genotype and our outcomes differ by HIV status by including interaction terms. Based on prior genetic association work in HIV-associated kidney disorders [83–89], we will test both additive and recessive genetic models.

### Specific aim 2

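### Aim 1 looks for sex differences only through separate analyses in men and women, which neither estimate nor test whether the HIV effect differs by sex; an HIV-by-sex interaction is needed

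*Protocol article*

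**What the plan says.** In the Protocol article, Specific aim 1, Statistical analysis plan, uACR is modelled by logistic regression (categorised) and by linear or cumulative probability models (continuous). The exposure is fixed: "HIV status is the primary exposure variable". Sex has a sentence of its own: "Primary analyses will control for sex and will be repeated among men and women, separately, to investigate potential differences by sex".

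Other possible modifiers are handled differently. The same paragraph states: "We will perform additional analyses to investigate the interaction between HIV status and individual risk factors, including hypertension and co-infection (HBV and CMV"). Power calculations for interaction effects (Table 5) gives detectable differences for hypertension. Genetic analysis plans will test whether *APOL1* associations "differ by HIV status by including interaction terms".

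No HIV-by-sex term, and no other formal comparison of the male and female results, is named. No power is given for a sex difference, and the expected proportion of men and women is not stated.

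**The concern.** The stated purpose is to look for a difference between the sexes, but the named method does not produce that quantity. Whether HIV acts differently in men and women is a question about the difference between two coefficients. Two separate models give each coefficient with its own uncertainty and leave the comparison to the reader.

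The usual risk is that an association significant in one sex and not in the other gets reported as a sex difference. Each stratum has less power than the whole sample, so that pattern can arise by chance when the HIV effect is identical in both. At stake is a secondary finding about sex. The main HIV estimate, which is adjusted for sex, is not affected.

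**Working it through.** **Inputs from the Protocol article (Aim 1, Sample size and Table 3).** 3000 HIV-positive and 750 HIV-negative participants, "at the alpha = 0.05 level (i.e., with a two-sided p-value < 0.05"), and "90% power to detect a relative risk for albuminuria between HIV-positive and HIV-negative participants of 1.19 (0.400 vs. 0.336, respectively").

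**Assumptions not in the document.** The sex split is not given. I take 50:50, with 60:40 and 70:30 as a range, and the same split in both HIV groups because the controls are sex-matched. The true HIV effect is set equal in men and women, so any apparent sex difference is spurious. A difference is taken to be read from significance in exactly one sex; the article states no such rule.

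**Step 1: reproduce the stated power.** Pooled two-proportion test without continuity correction:

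power = Φ[(|p1 − p0| − 1.96 × SE0) / SE1], with SE0 = √[p̄(1 − p̄)(1/n0 + 1/n1)] and SE1 = √[p0(1 − p0)/n0 + p1(1 − p1)/n1].

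With n0 = 750, n1 = 3000, p0 = 0.336 and p1 = 0.400: p̄ = 0.3872, SE0 = 0.01989, SE1 = 0.01943. Power = Φ[(0.064 − 0.03898)/0.01943] = Φ(1.288) = 0.901. The stated figure of about 90% reproduces. At 0.345 the power is 0.794 against the stated 80%, which also reproduces.

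**Step 2: power within each sex at an even split.** With n0 = 375 and n1 = 1500: SE0 = 0.02812, SE1 = 0.02748. Power = Φ[(0.064 − 0.05512)/0.02748] = Φ(0.323) = 0.627.

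**Step 3: chance that exactly one sex is significant.** With powers a and b in the two sexes, P = a(1 − b) + b(1 − a). At 50:50 this is 2 × 0.627 × 0.373 = 0.468.

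| True HIV-negative proportion (HIV-positive 0.400, same in both sexes) | 50:50 | 60:40 | 70:30 |
|---|---|---|---|
| 0.400 (no HIV effect) | 9.5% | 9.5% | 9.5% |
| 0.345 (Table 3, 80% power) | 50.0% | 51.3% | 54.9% |
| 0.336 (Table 3, 90% power) | 46.8% | 48.7% | 54.4% |
| 0.300 | 8.9% | 11.6% | 20.6% |
| 0.275 | 0.8% | 1.6% | 5.5% |

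The powers behind the 0.336 row are 0.707 and 0.531 at 60:40, and 0.773 and 0.420 at 70:30. The 0.275 row comes from the bolded row of Table 5 with the 10% hypertension prevalence assumed there: 0.9 × 0.25 + 0.1 × 0.50 = 0.275. For the continuous outcome at 0.132 SD the three splits give 46.7%, 48.6% and 54.1%.

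**Step 4: the interaction test under the same conditions.** In 200,000 simulated studies per scenario (0.336, 0.345 and 0.400 against 0.400; splits 50:50 to 70:30), a Wald test of the difference in log odds ratios between the sexes rejected in 4.9% to 5.0% of studies, whatever the common effect or split.

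**Step 5: how precise the interaction would be.** At an even split with 0.336 vs 0.400, the variance of the log odds ratio in one sex is 1/(375 × 0.336 × 0.664) + 1/(1500 × 0.4 × 0.6) = 0.01195 + 0.00278 = 0.01473. The difference between the sexes has SE √(2 × 0.01473) = 0.172. The 95% CI for the ratio of odds ratios therefore extends by a factor of exp(1.96 × 0.172) = 1.40 either way. The HIV odds ratio itself is only (0.400/0.600)/(0.336/0.664) = 1.32, so the interval is wide.

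**The case against.** A reader might infer that the plan will declare a false sex difference about half the time. The documents do not support that. Table 3 gives 0.336 as the proportion the study could just detect, not as the expected value, and the probability is close to its highest there. The HIV-negative prevalences in Table 5 imply larger HIV effects; under its bolded row the figure is 0.8% at an even split and 5.5% at 70:30. This part of the objection stands, and the 47% must carry its conditions.

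A reader might also infer that the sexes will be compared by which result is significant. The article states no such rule. Two independent estimates with confidence intervals can be compared properly, and the plan does not exclude this. That stands as well.

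It can further be said that a condensed article may leave the comparison to a fuller plan, and that its list of interactions is open-ended and could take in sex. This carries less weight. Sex is not in that list, and it has its own sentence with a different method, so this is a stated choice and not just an absent detail.

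Two limits remain. No hypothesis, Aim 1 outcome or power calculation concerns a sex difference, so the question is secondary. And a single HIV-by-sex term holds the other covariate effects equal in men and women, which separate fits do not; that is a reason to keep both.

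**Conclusion.** The point holds in a limited form. The only named method for sex differences yields no estimate or test of a difference, although the plan uses HIV interactions for hypertension, HBV, CMV and *APOL1*. This is true whatever the effect size.

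The size of the possible error is conditional. It reaches 47% to 54% over splits from 50:50 to 70:30 only if the common HIV effect is 0.400 vs 0.336 and a difference is read from significance in one sex alone. At an even split it is about 9% with no HIV effect or at 0.300 vs 0.400, and under 1% at 0.275 vs 0.400. An interaction test holds it at about 5% in the scenarios simulated. The sex splits and the reading rule are assumptions. The change is worth making, but the primary HIV comparison does not depend on it.

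**What to change.** Add an HIV-by-sex interaction to the Aim 1 regression models as a secondary analysis. Report the interaction estimate with its 95% CI, and base any statement that the HIV effect differs between men and women on that estimate. Keep the separate analyses in men and women, labelled as descriptive.

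This needs no further participants, visits or measurements. The cost is one additional analysis, with an interaction estimate that will be imprecise. The report should therefore say that a non-significant interaction does not show the effect to be the same in both sexes.

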#### Genetic analysis plans

We will determine the prevalence of *APOL1* risk alleles, comparing the 750 HIV-negative adults to our 3000 HIV-positive study participants, specifically comparing the proportions of each population (i.e., HIV-negative vs. HIV-positive) possessing 0, 1, and 2 *APOL1* risk haplotypes (G1 or G2). We will examine the association between *APOL1* genotype and uACR and eGFR, adjusting for sex, age, and HIV status. Furthermore, we will test whether the associations between *APOL1* genotype and our outcomes differ by HIV status by including interaction terms. Based on prior genetic association work in HIV-associated kidney disorders [83–89], we will test both additive and recessive genetic models.

### Specific aim 2

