In recently published data from our NIDDK-funded R3 study [13, 14] among PWH, ages 18–69 years who were on ART for ≥ 6 months, ~ 40% of 2500 enrolled participants had some level of persistent albuminuria. Why is albuminuria so common in this HIV-positive, ART-experienced population? We hypothesized that genetics play an important role, given the high prevalence of *APOL1* renal risk variants in West Africa [13, 14]. However, genotyping in the R3 study revealed lower than anticipated prevalence of the high-risk (HR) *APOL1* genotype (6.2%), which has been associated with kidney disease risk [13]. The high rates of albuminuria observed in the R3 study population likely reflect a mix of both reversible microvascular endothelial injury (inflammation driven) and non-reversible podocyte damage (irreversible and progressive to CKD). The current study is designed to evaluate additional potential contributors to the high observed rates of albuminuria observed in PWH in Nigeria. *APOL1* high risk genotype and traditional risk factors (e.g., hypertension, diabetes, smoking) do not fully explain the high rates of albuminuria in the R3 study population, although hypertension is likely to be a significant contributing factor. In a prior study in Nigeria, adults with high normal blood pressure (BP) (systolic blood pressure [SBP] 130–139 mmHg and/or diastolic blood pressure [DBP] 85–89 mmHg) had higher rates of microalbuminuria (12.9% vs. 4.1%) and cardiovascular disease risk factors than those with optimal BP. Sickle cell disease and sickle cell trait are also common, with sickle cell trait affecting 1 in 12 African Americans and nearly 300 million people worldwide [15–17]. Although sickle cell trait is often considered a benign condition, kidney manifestations may include impaired urinary concentrating ability, hematuria, and papillary necrosis [17–21]. Although the relationship of sickle cell trait to long-term CKD has not been firmly established, prior studies have showed a higher-than-expected prevalence of sickle cell trait among participants with end stage kidney disease (ESKD). [15, 22, 23]

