#### Study measures

*Demographic and clinical data elements* will be abstracted from medical record and by self-report at baseline and will be updated during every scheduled study visit.*Demographics*: age, sex, self-reported ethnicity (Hausa/Fulani, Igbo, Yoruba, Other (Specify)*Education*: not literate, primary, secondary, tertiary (university or other college).*Occupation*: employment status (and if employed; details to be obtained)*HIV transmission risk factors*: heterosexual activity, homosexual activity, transfusion, other, unknown*Date of HIV diagnosis (PWH only)*: date of first positive HIV test*Date of ART initiation (PWH only)*: defined as three or more active antiretrovirals from two or more drug classes*Dates of AIDS-defining illnesses (PWH only)*: defined per CDC list of AIDS-defining illnesses*Dates of comorbid disease diagnoses*: infections including TB (pulmonary and extrapulmonary), viral infections (HBV, HCV [Aim 1], Lassa fever, COVID-19, etc.), AIDS-defining illnesses; NCDs including hypertension, diabetes, sickle cell trait or disease, dyslipidemia, cardiovascular disease, cancer, liver disease, lung disease, depression, and bone mineral density abnormalities (including non-traumatic fractures).*Antiretroviral medication start/stop dates (PWH only)*: from clinical record and pharmacy data (evaluating current exposure as well as prior/current TDF, protease inhibitor use to determine cumulative exposure time).*Current medications*: all medications taken at least once daily for ≥ 30 days, including traditional medications.*Laboratory HIV data*: all CD4 cell count and viral load measurements (collected per standard of care)**.** SARS-CoV-2 testing will be performed per existing standard of care and results of all COVID-19 screening tests will be captured in the patients’ study medical record).

*Social and behavioral data* will be collected three times during study follow-up using the following scales, which are all available in both English and Hausa languages (Table 6).*Substance use:* The Alcohol, Smoking and Substance Involvement Screening Test (ASSIST) is a cross-cultural screening of recent and lifetime substance use [90].*Depression:* The 9-item Patient Health Questionnaire (PHQ-9) [91] screens for depressive symptoms.

**Table 6 Tab6:** Procedures for longitudinal cohort of HIV-positive (n = 1,000) and HIV-negative (n = 500) participants with normoalbuminuria to be followed for 30 months (n = 1500 total)

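### The APOL1 association models list sex, age and HIV status for adjustment but not ethnicity, which leaves them open to bias if risk genotype and albuminuria both vary by ethnic group

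*Protocol article*

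**What the plan says.** All of this comes from the protocol article.

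- **Genetic analysis plans (Aim 1).** The APOL1 models examine the association between "genotype and uACR and eGFR, adjusting for sex, age, and HIV status". Interaction terms with HIV status follow, and both additive and recessive codings are to be tested. The section does not refer back to another covariate list.
- **Statistical analysis plan (Aim 1), immediately before.** "Regression models will be adjusted for potential confounders, including age, ethnicity, smoking status, and BMI", with sex also controlled. This section is organised around a different exposure: "HIV status is the primary exposure variable".
- **Genetics specimen collection and genotyping.** The individual data to be held "include age, ethnicity, sex, occupation, weight, BMI" and further items, so ethnicity is collected. The assays named are for APOL1 and the sickle variants, with other loci only as exploratory work. Neither ancestry markers nor principal components are mentioned.
- **Study measures (Aim 2).** The categories appear here: "self-reported ethnicity (Hausa/Fulani, Igbo, Yoruba, Other (Specify".

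**The concern.** A confounder of a genotype–outcome association has to be related to genotype. An autosomal genotype is fixed at conception. Age and sex may improve precision, but they are not plausible common causes of genotype and outcome. HIV status could stand in for ancestry only so far as it happens to track it. Ancestry is the standard common cause, and self-reported ethnicity is the one measure of it that the article says it will collect. The list for the genetic models therefore leaves out the covariate that addresses population stratification, although the section before it regards ethnicity as worth adjusting for.

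If high-risk genotypes are more frequent in one ethnic group, and that group has more albuminuria for other reasons, the model without ethnicity attributes part of the group difference to APOL1. A null gene could then appear associated, or a real association could be enlarged, shrunk or masked, depending on the direction of the differences.

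**Working it through.** The article gives no sample size, power or effect size for the APOL1 analysis, so there is no stated figure to reproduce. The check asks how large the bias could be under explicit assumptions.

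**Inputs from the article**
- Sample: "comparing the 750 HIV-negative adults to our 3000 HIV-positive study participants", so N = 3750.
- High-risk genotype: 6.2% in R3 (Background).
- Albuminuria: about 40%, from "40% of 2500 enrolled participants had some level of persistent albuminuria" (Background), applied here to the whole sample.
- Two-sided alpha of 0.05, stated for Table 3 and assumed to apply here.

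**Assumptions, because the article gives no figures by ethnicity**
- Two ethnic groups, with a majority share w = 0.80.
- Minority-to-majority ratio k of high-risk genotype frequency.
- Albuminuria higher by d in the minority.
- No gene effect within either group.

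**Formulas**
- Genotype frequencies: g1 = 0.062 / (w + (1 − w)k) and g2 = k × g1.
- Albuminuria: a1 = 0.40 − (1 − w)d and a2 = a1 + d.
- Minority share among high-risk carriers: sH = (1 − w)g2 / 0.062.
- Minority share among low-risk participants: sL = (1 − w)(1 − g2) / 0.938.
- Albuminuria: aH = a1 + d × sH in carriers and aL = a1 + d × sL in the rest.
- The spurious difference is d × (sH − sL). It is zero if d = 0 or k = 1.
- Group sizes: 3750 × 0.062 = 232.5 and 3750 × 0.938 = 3517.5.
- Standard error: SE = √[aH(1 − aH)/232.5 + aL(1 − aL)/3517.5], and z = (aH − aL)/SE.
- False-positive rate: 1 − Φ(1.96 − z) + Φ(−1.96 − z).

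**No difference in either genotype or albuminuria (k = 1 or d = 0).** aH = aL, the odds ratio is 1.00 and the false-positive rate is 5%.

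**Twofold ratio, 10-point gap.**
- g1 = 0.062/1.2 = 0.0517 and g2 = 0.1033; a1 = 0.38 and a2 = 0.48.
- sH = 0.333 and sL = 0.191.
- aH = 0.413 and aL = 0.399, so the odds ratio is 1.06.
- SE = 0.0333 and z = 0.43, so the false-positive rate is 7%.

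**Fourfold ratio, 10-point gap.**
- g1 = 0.062/1.6 = 0.0388 and g2 = 0.155; a1 = 0.38 and a2 = 0.48.
- sH = 0.500 and sL = 0.180.
- aH = 0.430 and aL = 0.398, so the odds ratio is 1.14.
- SE = 0.0335 and z = 0.95, so the false-positive rate is 16%.

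**The same case from allele frequencies.** Risk-allele frequencies of 0.20 and 0.39 give high-risk genotypes of 0.20² = 4.0% and 0.39² = 15.2%. Overall that is 0.8 × 0.040 + 0.2 × 0.152 = 6.2%. The same steps give aH = 0.429, aL = 0.398, an odds ratio of 1.13 and a false-positive rate of 15%. Simulations of this case gave 16–17% for the recessive coding.

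**Additive coding in that case.**
- Covariance of allele count and albuminuria: 0.8 × 0.2 × (0.78 − 0.40) × 0.10 = 0.00608.
- Variance of allele count: 0.256 + 0.095 + 0.023 = 0.374.
- Correlation: 0.00608 / √(0.374 × 0.24) = 0.0203, so z = 0.0203 × √3750 = 1.24.
- The false-positive rate is about 24%. The simulations gave 25–26%.

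**Adding ethnicity.** The odds ratio returns to 1.00 and the rate to 5%. That holds by construction, because the confounding was made to act only through the variable then added. It does not show that self-reported ethnicity would remove all stratification in the real data.

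**The case against.** The strongest reply is that the Genetic analysis plans section never says that other covariates are excluded. The preceding section, under the same Aim 1 statistical considerations, says in general terms that regression models will adjust for ethnicity. The genetic list could be a shorthand on top of that. The article is also a condensed account and points to additional files that are not shown. This reading is possible, but it does not settle the matter. The general sentence belongs to models with HIV status as the exposure, and the genetic section states its own, different list. If ethnicity was meant to be included, the list is misworded and the same edit is needed.

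The second reply is that the consequence is hypothetical, and this stands. Recruitment is at one hospital in Kano, and the article gives no ethnic mix and no genotype or albuminuria rates by ethnicity. The size of any bias rests wholly on assumptions. A roughly fourfold genotype ratio together with a 10-point albuminuria gap is a sizeable pair of differences. An eightfold ratio with a 15-point gap pushes the rate to 60% (odds ratio 1.36), but nothing in the article makes that corner likely.

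A reader might infer four stronger claims that the article does not support:
- **That the APOL1 results will be false positives.** Bias needs both differences, and neither is documented.
- **That the plan states a causal null for APOL1 and then tests something else.** It states no null and speaks of association.
- **That every other Aim 1 model adjusts for ethnicity.** The text supports this only for the general regression models.
- **That the eGFR results, the APOL1-by-HIV interaction and the comparison of genotype prevalence by HIV status are distorted to a known degree.** None of these was computed. The prevalence comparison is descriptive and does not call for adjustment on this ground.

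The reply on importance also has weight. APOL1 is not part of any stated hypothesis, and HIV status is the primary exposure, so the main conclusions do not depend on these models.

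**Conclusion.** The point holds as a conditional weakness in a stated model. The adjustment set for the APOL1–uACR and APOL1–eGFR associations omits ethnicity, which the article collects and elsewhere treats as a potential confounder, and no other control for ancestry is named. If risk-genotype frequency and the outcome both vary by ethnic group, the estimate is biased. If either does not vary, it is not.

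For binary albuminuria under the recessive coding, plausible assumed differences move the false-positive rate from 5% to between 7% and about 16%, with spurious odds ratios of 1.06 to about 1.14. The additive coding is more exposed in the one case worked. These figures assume two ethnic groups with a 20% minority and no true gene effect. For eGFR and continuous uACR the same logic applies, but no size is claimed. The change is worth making because it is nearly free, not because a bias has been shown.

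**What to change.** In Genetic analysis plans, add self-reported ethnicity to sex, age and HIV status as adjustment variables for the APOL1–uACR and APOL1–eGFR models and for their HIV-interaction versions. Use the categories already listed under the Aim 2 Study measures.

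The cost is a change of wording and, with four categories, three degrees of freedom out of 3750 participants. No new field is needed for new enrolments. The team should confirm that ethnicity is also on file for R3 participants who are not called back. Self-reported ethnicity is a coarse proxy for ancestry, and the listed categories combine Hausa and Fulani, so the report should acknowledge that some stratification may remain.
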